Based on the results of the systematic review of strategies for the transfer and social appropriation of knowledge, on the results of formal consensus of experts, and on the theoretical foundations of neurocognition and neuromarketing, the design of health knowledge capsules will be developed together with experts in health psychology, promotion and prevention in health, as well as experts in diagramming and development of audiovisual products. During this phase the final scripts, the graphic outline of the clips, their duration, the soundtrack and the production will be created, based on the results of the previous phases.

1. **Phase 5. Evaluation of effectiveness of knowledge capsules in terms of social appropriation of knowledge.**

A neuromarketing strategy will be applied in the Cognitive Neuroscience and Communication Laboratory of the National University of Colombia, with the objective of evaluating the effectiveness of the knowledge capsules in maternal and neonatal health in terms of social appropriation of knowledge, using measurements of attention, emotional response and remembrance.

The analysis will be conducted to find differences between subgroups or categories of educational level, defined as follows:

0 = No study

1 = Primary or Baccalaureate (basic education or secondary education)

2 = Higher Education (undergraduate and postgraduate)

*- Design:* Cross-over experimental study in which a group of pregnant women, non-pregnant women and adult men will be exposed to 13 clips, 12 of which will be produced through this knowledge transfer strategy and one will be an unrelated standard video that will be used as a control. The order of viewing the videos will be assigned randomly for each subject, so that each subject will have 13 evaluations. The random allocation tables will be generated by computer, and one will be made for each educational stratum (without education, with primary or secondary education, and with post-secondary education) and group (pregnant woman, non-pregnant woman and man). It is expected to have a minimum sample of 150 subjects.

*- Population and sample:*

- Inclusion criteria:

Pregnant women, non-pregnant women and men over 18 years of age, who agree to participate in the study through informed consent.

- Exclusion criteria:

participants who presented serious health problems linked to pregnancy or who presented any clinically significant visual and auditory problems, which affected the viewing of the videos.

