*- Type of sampling:* not probabilistic, for convenience.

*- Sample size:*

Using the statistical analysis program for biomedical, social and behavioral sciences G * Power 3, the sample size was calculated for a one-way analysis of variance (ANOVA) design and fixed effects, using the F statistic. The selection of the parameters was made for the recall outcome, expecting that the differences of the capsules compared with the video control would be moderate. The parameters were therefore defined as follows: moderate effect size f = 0.3; power (1-β) = 0.90 and alpha (α) = 0.05 for three groups. The calculation yielded a result of 144 for the total sample. Considering that there would be no follow-up of the participants and the measurements would be taken in a single session, a low number of losses was estimated (mainly due to failures in the registry), so a minimum of 150 subjects was defined as a total sample, 50 for each group.

*Process:*

All participants will sign an informed consent (Annex 1) after explaining the objectives of the study and procedures that will be carried out. Participation will be completely voluntary.

The procedure consists of the projection of 12 health knowledge capsules of approximately 35 seconds each, and a control clip, not related to the subject. The control clip will be a standard video, which provides information on reproductive health and maternal safety, but which has not been designed based on evidence or following strategies based on neuromarketing.

The observation of the videos will be free; that is, they will not be explained to the participants during the screening, or the content of them. All the videos will be seen by the participants, but the observation of each one will be assigned in a random way.

The successive order of visualization of the videos is presented in Figure 1. It shows the successive ordering of the clips. However, the actual order of visualization of the clips will be done randomly for each of the subjects.

[figure not shown]

***Figure 1.*** *Form in which the assignment and evaluation of the effect of each intervention is planned.*

The process of consolidating results will be done for each clip as shown in Figure 2.

***Figure 2.*** *Selected sample, and methodological format of analysis of the clips*

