***Statistic analysis:***

Hypotheses raised:

- **Study hypothesis 1**

Comparison between capsules and video control

H0: μ capsule X = μ video control

Ha = μ capsule X ≠ μ video control

*μ = average attention, emotional reaction and recall*

- **Study hypothesis 2**

Comparison between groups: men, non-pregnant women, pregnant women

H0: μ1 = μ2 = μ3

Ha: ∃μj ≠ μ j = 1, 2, 3

*μ = average attention, emotional reaction and recall*

- **Study hypothesis 3**

Comparison between levels of schooling: none, primary, baccalaureate, undergraduate, postgraduate

H0: μ1 = μ2 = μ3

Ha: ∃μj ≠ μ j = 1, 2, 3, 4, 5

*μ = average attention, emotional reaction and recall*

- **Study hypothesis 4**

Comparison between family history: children, no children

H0: μ1 = μ2

Ha: μ1 ≠ μ2

*μ = average attention, emotional reaction and recall*

A descriptive analysis of the measured variables will be carried out. The qualitative variables will be described in proportions, and calculations for averages and standard deviation that follow a normal distribution will be performed for quantitative variables. For variables that do not follow this distribution, medians and interquartile ranges will be calculated. The normality of the variables will be evaluated by the Shapiro-Wilk test.

The difference between the averages of the variables of emotional reaction and attention will be carried out by means of an analysis of variance (ANOVA) for dependent samples, taking into account the effect of drag. For these comparisons, the non-parametric tests of Kruskal Wallis and the Wilcoxon rank sum will be used, according to the number of levels of each factor.

For the results of the survey, in which the recall of the contents of the capsules will be evaluated after their screening, an analysis will be made to compare the difference in proportions between the groups with a good level of recall and those with a low level of recall for each category of educational level.

Statistical software Stata 13.1 will be used to analyze the data.

1. **Phase 6. Final production of the health capsules in maternal and neonatal safety**

Professional experts in the layout and development of audiovisual animation products will carry out the final production process, taking into account the changes suggested by the analysis of results of the neuromarketing strategy.

- - - 1. **Ethical considerations**

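### The comparisons of men, non-pregnant and pregnant women, and of people with and without children, are open to confounding by age, and the protocol states no age term

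*Protocol*

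**What the plan says.** Under Phase 5, Population and sample, the protocol admits "Pregnant women, non-pregnant women and men over 18 years of age", subject to their consent. The wording leaves open whether the lower limit covers all three groups or only the men; either way there is no upper limit. The exclusions contain no age rule: they remove "participants who presented serious health problems linked to pregnancy or who presented any clinically significant visual and auditory problems".

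Sampling is "not probabilistic, for convenience", with 50 participants planned per group and no age quota or matching. The random tables are stratified, since "one will be made for each educational stratum (without education, with primary or secondary education, and with post-secondary education) and group", but they assign the order of the videos. They do not balance people between groups, and age is not a stratum.

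Under Statistic analysis, hypothesis 2 is a "Comparison between groups: men, non-pregnant women, pregnant women" and hypothesis 4 compares people with and without children. In both, the quantity compared is "μ = average attention, emotional reaction and recall". The stated methods are an analysis of variance for dependent samples and a second set of methods, given as follows: "the non-parametric tests of Kruskal Wallis and the Wilcoxon rank sum will be used, according to the number of levels of each factor". For recall, proportions are compared. No age term appears.

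**The concern.** Being pregnant, being male or having children cannot be randomised. Only restriction, matching or adjustment can separate these characteristics from age, and the protocol states none of them for age. The rank tests it names take no covariate.

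The eligibility rule is also asymmetric. Pregnant women fall within child-bearing ages by definition, while men and non-pregnant women may be of any adult age. Convenience recruitment could therefore bring in older men and women with no age counterpart among the pregnant women. If attention measures, electrodermal response or recall vary with age, part of a group difference would be an age difference. Hypothesis 4 is exposed in a related way, because the chance of having had children accumulates with age.

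Phase 6 revises the capsules in the light of this analysis. A difference read as a response to pregnancy, sex or parenthood could therefore shape the final product when age explains part of it.

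**Working it through.** **The plan's own figure.** Sample size section: one-way fixed-effects ANOVA, three groups, f = 0.3, α = 0.05, power 0.90, stated total 144. The test has noncentrality λ = N·f² and degrees of freedom (2, N − 3).

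- N = 144: λ = 144 × 0.09 = 12.96, power 0.9008. N = 141 gives 0.8941. The stated 144 reproduces.
- N = 150, as planned: λ = 150 × 0.09 = 13.5, power 0.913.

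The concern does not depend on this figure. The same test serves for the illustration below.

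**Where age can enter.**

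- Hypothesis 1: every participant sees all 13 clips, so each person is their own control. Age differences between people do not confound capsule against control.
- Hypotheses 2 and 4: the contrasts are between different people in groups that are not randomised, with no stated control for age. Age can confound both.

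**Illustration.** From the protocol: N = 150, 50 per group, α = 0.05. Assumed, with no source in the protocol:

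- no true group effect;
- both other groups older than the pregnant women by the same mean gap of 5, 10 or 15 years;
- a linear age trend of 0.01, 0.02 or 0.03 SD per year;
- a single outcome with within-group SD 1, tested by a one-way F test.

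The spurious shift is d = slope × gap. The group means are (0, d, d), so f = d·√2/3, and λ = 150·f².

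Worked case: gap 10 years, slope 0.02. Then d = 0.20, f = 0.20 × 0.4714 = 0.094, λ = 150 × 0.00889 = 1.33, and the test rejects 16.0% of the time.

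Probability of rejection with no true group effect (nominal 5%):

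| Mean age gap | 0.01 SD/year | 0.02 SD/year | 0.03 SD/year |
|---|---|---|---|
| 5 years | 5.6% (d = 0.05) | 7.5% (d = 0.10) | 10.9% (d = 0.15) |
| 10 years | 7.5% (d = 0.10) | 16.0% (d = 0.20) | 31.6% (d = 0.30) |
| 15 years | 10.9% (d = 0.15) | 31.6% (d = 0.30) | 62.9% (d = 0.45) |

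The direction of the age trend does not matter to this two-sided result. With no gap or no trend, the rate stays at 5%.

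**The case against.** The strongest reply is that the main question is untouched. The overall objective is the effectiveness of the capsules, and the sample size parameters were chosen for capsules against the control video, which is a within-subject comparison. That stands, and it limits the point to secondary comparisons in a pilot study.

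The second reply is that an open upper age suits the stated audience. The Problem Statement addresses the general population and the families or companions of pregnant women. A common age window would make the groups more alike but would lose older relatives who belong to that audience. This also stands, so the eligibility rule itself should not be counted as an error.

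Third, the illustration takes its slope and age gap from outside the protocol, and it uses a one-way F test on one outcome where the protocol names other tests. That is correct. A 5-year gap gives only 5.6% to 10.9%, and the top figure needs the largest gap and the steepest slope together.

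Fourth, covariates are commonly left to a statistical analysis plan, which is not shown here and might already include age. What remains is that the protocol does name tests for these hypotheses, and those tests, followed as written, make no allowance for age.

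A reader might infer more than this. The eligibility rule does not create an imbalance; it allows one. Nor would an imbalance be beyond repair, since hypothesis 2 can be analysed within the ages that all groups share. Hypothesis 2 also asks only whether the group means differ. The protocol does not say that a difference will be attributed to pregnancy or sex. Finally, the open upper limit is not the cause of the problem in hypothesis 4, because parenthood would still vary with age inside any common window.

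**Conclusion.** The point holds as a modest one. As the protocol is written, hypotheses 2 and 4 compare non-randomised groups that may differ in age, with no stated control for it, so a difference may reflect age in part or in whole. Hypothesis 1 is not affected.

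The size of the bias is unknown, because the protocol gives no age distribution and no age effect. Across the assumed range, false rejection for hypothesis 2 runs from close to nominal (about 6%) to serious (about 63%). No size was computed for hypothesis 4. The case for acting rests on how little the remedy costs, not on a demonstrated large bias.

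**What to change.** Leave the inclusion criteria as they are. Record each participant's age, which has to be established at entry in any case. For hypotheses 2 and 4, replace the unadjusted tests with a regression or ANCOVA that includes age as a covariate. Where recall is analysed as good or low, use the logistic equivalent. For hypothesis 2, add a sensitivity analysis restricted to the age range represented in all three groups, because covariate adjustment outside that range relies on extrapolation.

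The cost is slightly more analysis work and a smaller sample, hence less precision, in the restricted analysis. The planned total of 150 does not change, and older relatives stay in the study.

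### The stated 90% power comes from a comparison of three independent groups, but its effect size is justified by the within-subject capsule-versus-control difference, for which power is not established

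*Protocol*

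**What the plan says.** The Phase 5 sample-size section states that "the sample size was calculated for a one-way analysis of variance (ANOVA) design and fixed effects, using the F statistic". The inputs are "moderate effect size f = 0.3; power (1-β) = 0.90 and alpha (α) = 0.05 for three groups". The rationale, given just before them, concerns recall: "expecting that the differences of the capsules compared with the video control would be moderate". The result follows: "The calculation yielded a result of 144 for the total sample". A small allowance for recording failures is then added, and "a minimum of 150 subjects was defined as a total sample, 50 for each group".

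The Phase 5 design section describes a cross-over study. Each participant watches 12 capsules and one control clip in random order and so contributes 13 evaluations. The participants are pregnant women, non-pregnant women and men. The same phase defines three education categories and prepares the random allocation tables within them.

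The Phase 5 statistical analysis section lists four hypotheses and calls none of them primary. The first is headed "Comparison between capsules and video control". The second compares the three population groups. The third is headed "Comparison between levels of schooling: none, primary, baccalaureate, undergraduate, postgraduate", which is five levels. Attention and emotional reaction are to be analysed by ANOVA for dependent samples. Recall is to be analysed as a difference in proportions (good versus low recall) by educational level.

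**The concern.** The effect size and the sample size answer different questions. The reason given for f = 0.3 is a difference between clips, with each person serving as his or her own control. The calculation that uses f = 0.3 compares three sets of different people. The only three groups of 50 in the protocol are the population groups, so the 144 fits hypothesis 2 while its rationale belongs to hypothesis 1.

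Two things follow. Nothing supports f = 0.3 as a difference between pregnant women, non-pregnant women and men. And no power or detectable difference is given for capsule versus control, although evaluating the capsules is the stated objective of the phase. A reader who sees 90% power beside the capsule-versus-control rationale could take a null capsule result for a negative finding at 90% power, which the calculation does not warrant.

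**Working it through.** **Inputs from the protocol (Phase 5).** f = 0.3, alpha = 0.05, power 0.90, k = 3, N = 144 raised to 150 (50 per group), 13 evaluations per subject, 12 capsules each set against one control.

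**Inputs the protocol does not give (assumed).** Within-subject correlation rho, shown from 0 to 0.7. Any adjustment for 12 comparisons, shown as none and as 0.05/12 = 0.00417.

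**1. Reproduce the stated figure.** For a one-way fixed-effects ANOVA with k equal independent groups, the F statistic has k − 1 and N − k degrees of freedom and noncentrality lambda = N·f².

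- N = 141: lambda = 141 × 0.09 = 12.69, power 89.4%.
- N = 144: lambda = 144 × 0.09 = 12.96, power 90.1%.
- N = 150: lambda = 150 × 0.09 = 13.50, power 91.3%.

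So 144 is the smallest balanced total for k = 3. With the same f, alpha and power, other numbers of independent groups give other totals: 120 for k = 2, 180 for k = 5 and 260 for k = 13. The figure belongs to three independent groups.

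**2. Capsule versus control with 150 subjects.** For a continuous outcome and one capsule against the control, a paired t-test has 149 degrees of freedom and noncentrality dz·√150. Here dz = d/√(2(1 − rho)), and d is the mean difference in units of the raw SD. The word "moderate" can be carried over in two ways:

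- As Cohen's f = 0.3 for two conditions: d = 2f = 0.6.
- As a difference of 0.3 raw SD: d = 0.3.

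With rho = 0, dz = 0.6/√2 = 0.424 or 0.3/√2 = 0.212.

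| d | rho | dz | Power, alpha 0.05 | Power, 0.05/12 |
|---|---|---|---|---|
| 0.6 | 0 | 0.424 | 99.9% | 98.8% |
| 0.3 | 0 | 0.212 | 73.3% | 38.1% |
| 0.3 | 0.3 | 0.254 | 87.0% | 57.8% |
| 0.3 | 0.5 | 0.300 | 95.5% | 77.6% |
| 0.3 | 0.7 | 0.387 | 99.7% | 96.5% |

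For d = 0.6, a positive correlation only raises the power further. Across these readings the power runs from 38% to nearly 100%, and the protocol does not say where in that range the study lies.

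**3. Detectable paired difference.** Solving the same formula for 90% power with 150 pairs gives dz of about 0.27 at alpha 0.05 and about 0.34 at 0.05/12.

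**4. Recall.** This is the outcome chosen for sizing, yet it is to be compared as proportions. Neither the ANOVA of means nor the paired t-test above is that analysis. A paired comparison of dichotomised recall depends on the discordant proportions, which are not given, so no figure can be computed.

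**5. Education (hypothesis 3).** At N = 150, f = 0.3 and equal group sizes, power is 91.3% for three levels. For five levels lambda is still 13.50, but the F statistic has 4 and 145 degrees of freedom, and power is 83.9%.

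**The case against.** The strongest reply is that the trial is not harmed. If the protocol's own f = 0.3 is moved to two conditions it becomes d = 0.6, and 150 subjects give at least 98.8% power even with no correlation and a twelvefold adjustment. This stands. A reader might infer from the mismatch that the study is too small for hypothesis 1, but the protocol does not support that. The low figures need a smaller reading of "moderate" together with low correlation, an adjustment, or both. In particular, the 77.6% in the table treats 0.3 as a paired standardised difference, which is a different scale from Cohen's f, and it adds an adjustment that the protocol does not state.

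A second reply concerns education. A reader might infer that hypothesis 3 falls short of the stated power. That holds only for five levels. The design section defines and stratifies on three, and the null hypothesis written for hypothesis 3 also has three means. With three balanced levels, power is 91.3%. Convenience sampling makes balance uncertain in either case. What stands is the conflict between three and five.

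A third reply is that no hypothesis is labelled primary, that the work is called a pilot study, and that the text does say three groups of 50, so the layout used is visible. This is correct, and it is why capsule versus control should not be called the main hypothesis as if the protocol had said so. It does not remove the fault, because the paragraph itself ties its parameters to that contrast.

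**Conclusion.** The point holds as a mismatch between justification and calculation; there is no arithmetic error. The 144 (150) subjects and 90% (91.3%) power apply to an omnibus comparison of three equal independent groups at f = 0.3, an effect size that the protocol does not justify for those groups. They do not apply to the within-subject capsule-versus-control comparison, nor to the planned comparison of recall proportions.

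Power for hypothesis 1 is not established, and this is neither adequacy nor inadequacy. For one continuous outcome and one capsule it lies between 38% and nearly 100%, depending on how "moderate" is scaled, on a correlation assumed between 0 and 0.7, and on whether 0.05 or 0.05/12 is used. The correlation and the adjusted level are assumptions made here.

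**What to change.** Keep 150 subjects and restate the Phase 5 sample-size section:

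- **Hypothesis 2.** Say that 144 subjects (90%) and 150 subjects (91.3%) refer to an omnibus comparison of three equal independent groups at f = 0.3, and justify that effect size for pregnant women, non-pregnant women and men.
- **Hypothesis 1.** State the paired difference detectable with 150 subjects. For continuous outcomes at 90% power this is a standardised paired difference of about 0.27 at alpha 0.05, or about 0.34 if a 0.05/12 adjustment is adopted. Label the alpha level and any correlation used as assumptions.
- **Recall.** State the detectable difference on the scale on which recall will be analysed. If it is dichotomised and compared within subject, give the assumed discordant proportions.
- **Hypothesis 3.** Reconcile the three education categories of the design section with the five in the hypothesis list, and state the power for the number kept (150 subjects, balanced, f = 0.3: 91.3% for three, 83.9% for five).

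The cost is one rewritten paragraph and one settled definition of education. No participants are added and the design does not change. If five education levels are kept, the power stated for that comparison becomes less favourable.

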During the screening of the health knowledge capsules, the eye tracking method will be applied to evaluate the attention of the subjects before the visual stimulus of the health capsules. By means of a Tobii TX 300 eye tracker and the Tobii Studio Software, the pupillary size in arbitrary units (AU), and the duration and direction of the fixation in seconds will be measured. Areas of interest will also be recorded, according to the stimuli in which the attention is fixed, the duration, and the order in which the visual exploration is performed.

The monitoring of the autonomous activity will be carried out through the registration of the electrodermal activity (Galvical Skin Reaction), which allows the evaluation the state or emotional reaction of the subjects. The record of electrodermal activity will be measured by the computerized psychophysiological recording equipment I-330-C2 + 12. (J & J Enterprises Seattle, WA). The measuring electrodes will be placed on the distal phalanx of the third and fourth finger of the non-dominant hand with SE-35 sensors connected to a T-601 preamplifier (J & J Enterprises Seattle, WA). For the analysis of results, the USE3 Software from Physiolab will be used (J & J Engineering, 2004).

The analysis of skin conductance data will be carried out with a procedure performed by Benedek and Kaernbach, through which the amplitude of the electrodermal response to a stimulus is obtained. Thus, two register values ​​will be recorded to calculate the amplitude: the conductance recorded in the lowest time of the latency period and the conductance peak. Subsequently, these values ​​and their registration will be subtracted. This analysis will be performed for each event identified in each capsule by each subject, to obtain an average of the conductance amplitudes for each grouping of images-events (positive, negative and neutral).

Between each video there will be a break of 5 to 10 seconds, and before starting the next video for evaluation there will be a neutral sequence in order to calibrate the response of the individual to a neutral state: this is considered to be the washout period between each video.

A parametrization of the measurements will be carried out in order to be able to relate both variables. Subsequently, a survey will be applied to evaluate the recall component.

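### The electrodermal amplitude rule does not separate overlapping responses within a clip, so emotional-reaction scores can depend on how events are spaced

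*Protocol*

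**What the plan says.** In Protocol Phase 5, under Process, skin conductance is to be analysed by a named published procedure, "through which the amplitude of the electrodermal response to a stimulus is obtained". The text then spells out the calculation. Two readings are taken, "the conductance recorded in the lowest time of the latency period and the conductance peak", and these values "and their registration will be subtracted".

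On the unit of scoring it says: "This analysis will be performed for each event identified in each capsule by each subject". The amplitudes are then averaged within three classes of event: positive, negative and neutral. The material shown is "12 health knowledge capsules of approximately 35 seconds each", plus one control clip.

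The only return to a neutral state is between clips: "Between each video there will be a break of 5 to 10 seconds", followed by a neutral sequence that the protocol treats as its washout. Nothing comparable is described between events inside a clip. The number of events per clip, their spacing and the rule for locating the peak are not given.

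Under Statistic analysis, hypothesis 1 compares each capsule with the control on attention, emotional reaction and recall. Its null hypothesis is "μ capsule X = μ video control".

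**The concern.** Peak minus latency trough recovers the size of a response only if the previous response has died away. If it has not, the earlier response keeps falling while the new one rises. That fall is taken off the new rise, and the score comes out too small. If events are so close that responses merge, one event can instead be credited with part of its neighbour's rise.

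Either way, the error depends on how events are placed in the clip and how strong the preceding event was. These are properties of the clip, shared by everyone who watches it. Randomising the order of clips does not change the order of events inside a clip, and a larger sample only estimates the distorted mean more precisely.

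Two results are exposed. One is the capsule-versus-control comparison of emotional reaction. The other is the set of averages by positive, negative and neutral event, because a mild event after a strong one loses the larger share of its amplitude. Phase 6 then revises the capsules on these results.

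The protocol already treats residual response as a problem between videos: it inserts a neutral sequence and says the ANOVA will allow for carry-over. Within a clip, where events are closest together, it makes no such provision.

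**Working it through.** The protocol states no figure for electrodermal amplitude or event density, so there is none to reproduce. Its sample size was set on recall and does not enter here.

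**Inputs from the protocol.** Clip length is about 35 s. The score is peak minus the lowest value in the latency period, taken per event and averaged. I take the control clip to be scored in the same way, since hypothesis 1 needs a control value.

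**Assumed inputs (not in the protocol).** Each response has the shape g(x) = exp(-x/τ2) - exp(-x/τ1), scaled to a peak of 1. The pairs (τ1, τ2) are (0.75, 2), (0.75, 4), (1, 4), (0.75, 8), (1, 8) and (1, 12) s. Latency is 1.5 s. All true responses are equal and evenly spaced. The trough is the minimum from 1 to 2.5 s after the event.

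**One pair by hand**, with τ1 = 0.75, τ2 = 2 and events 4 s apart:
- Time to peak: [0.75 × 2 / (2 - 0.75)] × ln(2/0.75) = 1.18 s. Unscaled peak: 0.555 - 0.208 = 0.347.
- Earlier response when the second one starts: g(4)/0.347 = (0.1353 - 0.0048)/0.347 = 0.376.
- Earlier response at the second one's peak: g(5.18)/0.347 = (0.0751 - 0.0010)/0.347 = 0.214.
- Fall subtracted from the new rise: 0.376 - 0.214 = 0.162.
- Score for an equal second event: about 1 - 0.162 = 0.84. Full simulation gives 0.85, because the summed curve peaks slightly earlier.
- Score for a second event half as strong: about (0.5 - 0.162)/0.5 = 0.68 of its true size (simulation 0.71). The absolute loss is about the same, so the proportional loss roughly doubles. At 6 s spacing the simulated loss for this shape is 12%.

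**Whole clip.** Mean score as a percentage of the true amplitude, range over the six shapes, under two possible peak rules:

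| Events in 35 s | Spacing (35/n) | First local peak after trough | Highest value up to 6.5 s after event |
|---|---|---|---|
| 3 | 11.7 s | 92-100% | 92-100% |
| 6 | 5.8 s | 78-94% | 78-94% |
| 9 | 3.9 s | 66-84% | 78-95% |
| 12 | 2.9 s | 53-73% | 70-94% |

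Up to 6 events the peak rule makes no difference. From 9 upward it does. For the slowest shape (1, 12), the second rule gives 78% at 6 events, 95% at 9 and 116% at 17, so the score rises as events get denser.

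**Second coding with different windows** (decay constants 2 to 20 s). The loss is about 1-23% at 4 to 10 s spacing and 0-5% at 15 s or more. Over-reading appears at very close spacing: 1.28 times the truth at 1 s with 8 s decay, and 1.29 at 2 s with 20 s decay.

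**What a difference between clips would do.** If one clip had 3 events and another 6, the ratio of scores for equal true reactions would be 0.94/1.00 = 0.94 for the fastest shape and 0.78/0.92 = 0.85 for the slowest. That is a spurious gap of about 6% to 15%. The 3 and 6 are illustrative; the protocol gives no counts.

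**The case against.** The strongest reply is that the protocol names a published procedure, and the two-value sentence may only be a loose, translated summary of it. Whether that procedure separates overlapping responses cannot be judged from the protocol, so it would be wrong to say that the procedure lacks such a step. What stands is narrower: the calculation actually written out is a plain subtraction, and an analyst who follows it would do just that.

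Second, event count and spacing are nowhere stated, and scripts and durations are still to be created in Phase 4. With three well-spaced events the loss is at most about 8%. This is correct, and it makes the size conditional.

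Third, equal under-reading in every clip creates no difference between clips. Hypothesis 1 is biased only if event spacing or sequence differs between a capsule and the control. The protocol does not show that it differs. Nor does it prevent it: the control is an existing type of video not built on the same design principles, and no matching of events is required. For hypotheses 2 to 4 the objection largely succeeds, because the viewer groups see the same 13 clips and a shared proportional loss mostly cancels.

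Fourth, a reader might infer that clips with denser events always score lower. The calculation does not support this. Beyond about 6 events per clip the result turns on the unstated peak rule, and with slow recovery the direction can reverse.

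Finally, signal-scoring details are often left to an analysis plan. Here, however, the protocol fixes the scoring rule itself, so the rule can be assessed as written.

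**Conclusion.** The concern holds in a limited form. As written, the amplitude rule is open to an overlap error that depends on event spacing, which the protocol does not fix. Under the assumed response shapes and equal true responses, the mean score is about 92-100% of the truth at 3 evenly spaced events per clip and 78-94% at 6. For closer events neither size nor direction can be given without a peak-search rule.

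The error can bias the capsule-versus-control comparison of emotional reaction, and the positive, negative and neutral averages, whenever spacing or sequence differs between clips. The documents do not establish that such a bias will occur, that it always runs downward, or that the named procedure is itself at fault. Electrodermal response is one of three outcome measures, and recall and eye tracking are untouched. The change is worth making because it is cheap and because neither randomisation nor sample size protects against this error.

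**What to change.** In Phase 5, under Process, replace the two-value subtraction with a decomposition of the conductance trace into tonic and phasic activity that separates overlapping responses. Take as each event's amplitude the phasic response attributed to it in one post-onset window, fixed in advance and identical for all 13 clips. Then average by event class as planned. State also how two events that fall within one window are handled, since a fixed window alone does not settle that case.

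Reconcile this with the named procedure. If it already separates overlapping responses, say that its output is the amplitude and delete the sentence describing the subtraction.

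The cost is one extra off-line processing step on recordings already planned, possibly outside the named software, and a window to choose beforehand. No new equipment, visits or participants are needed.
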